### 4.3 Focus group

Upon the course termination, we conducted a focus group with three students enrolled in the course, three of the professors of the course, and three investigators related to the field of palliative care to discuss the experience of the participants. A thematic content analysis of the focus group transcription is yet to be carried out. In the meantime, the field notes of two of the researchers in the focused group were examined to obtain an initial overview of topics discussed on the focus group (S3 File).

Among the points that students highlighted during the conversation, three stood out: (1) the number of people per group, (2) the feelings aroused by the classes, and (3) the usefulness of the material learnt. Two of the students that attended the focus group agreed that the size of the class was crucial for them to feel more comfortable speaking about the issues discussed during the course. This claim was also supported by two of the professors. Furthermore, the three students mentioned that the topic of the class and the class material generated a wide variety of feelings. There were also some comments about the importance of managing said feelings and giving the students resources to cope with those emotions as well. And, finally, all of them found the content of the class useful and applicable to their day-to-day life. An emphasis was made on the communicational aspects of the syllabus and the practical guidelines for caring for other people.

Regarding the input from the professors, the perspectives were more diverse as their tasks within the course were different. Two of them gave theory classes in the Module 2, where the groups where smaller; and the other one gave the Module 4 class with the full class. Yet, there were some areas of common ground. The three professors found this course to be challenging, either because of the difficulties in communicating to an audience unrelated to the health sector or because of the complexity of the content itself. Additionally, a recurrent topic during the conversation was the diversity of profiles among the students, as they all came from different degrees. In relation to this diversity, two of the professors mentioned that one of the things they enjoyed most of the experiences was reading the students insights, thoughts, and reflections. Lastly, two of the professors also pointed out that the course evoked a feeling of a shared experience with the students.

## 5. Discussion

In the first year of the Teach-Inn Pal project, the protocol proposed an assessment method to evaluate the effectiveness of the course in transmitting the palliative care message to people beyond the health sector. This protocol also assessed the course capacity to create ambassadors of palliative care who can generate new frameworks for dialogue within society. To respond to these propositions, we identified two research questions that will be discussed below.

### 5.1 Research question 1: Is educational innovation a suitable solution to the communication necessities of palliative care?

We believe that this approach is innovative as it averts the usual health promotion programs, in which the information moves on a one-way flow from the sender to the recipients and is heavily dependent on the media as a channel [9, 24]. This social intervention shifts the trajectory in the dissemination of palliative care knowledge to society. Rather than transferring knowledge on a hierarchical basis, it is a designed to be an extended experience that allowed students to witness what care looks like and have dialogues with professionals dedicated to caring.

By doing so, not only do we involve the students in their own learning, but we also provide them with the opportunity to redirect and adapt the syllabus to fit their needs. We thus ensure that students value their learning, which may result in said learning becoming perdurable and worthy of being retransmitted. Educational innovation seems to be a tailored solution to the communication necessities of palliative care, as it strives to leave a long-lasting impression on students, ensuring that the palliative care message is well embedded on the recipients.

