### 2.3 Care and Society course structure

#### 2.3.1 Module I: Transformative learning

In this module, through flipped classes, the students will receive the theory required to face the rest of the course. The students will learn to identify situations of serious illness that involve intense suffering, and to outline a set of actions that help to care for the person suffering. During this segment, the total of students will be divided in three groups to encourage participation and to adapt the class to the necessities of everyone. The groups will switch professors every two weeks, as each professor will oversee the explanation of a set of topics related to one of three categories: cancer, dementia, and neurodegenerative illnesses.

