#### 3.4.2 Moment 2: Learning assessment

Following the end of Module I, students will receive links to the PCKQ and TECA of Moment 2. Furthermore, to evaluate Module II for teaching purposes, a ten-minute debriefing will be recorded at the end of the Escape Room. With their written consent, transcripts of this recording will be used to help analyze the data.

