### 4.1 Palliative Care Knowledge Questionnaire

The students were asked to complete a PCKQ in three different moments of the course: before it started (Moment 1), after the first module (Moment 2), and during the last class (Moment 3). The PCKQ included four multiple choice questions with multiselect answer options, in which students were asked to pick the options that best described palliative care, and one open question in which students were asked to define palliative care. From the 25 students that accepted to participate, 12 students responded in Moment 1, 25 responded in Moment 2 and 21 responded in Moment 3.

The analysis carried out is centered on the open question and only took into consideration respondents who answered at the 3 Moments (S1 File). Although some of the students appear to have a vague knowledge on palliative care, when asked to define palliative care in Moment 1, the answers revolved around the idea of the final moments of the patient. The definitions made use of concepts such as “terminal”.

“The care and support received by terminally ill patients and their families”,P1.“It is a treatment that is carried out in very specific and extreme circumstances to provide the patient with a state of well-being and tranquility, avoiding the pain without cure”,P2.“Accompanying terminally ill people”,P3.

In Moment 2, we start to see a shift in perspective. While students still made use of words like “terminal” in the definitions, the answers were no longer focused on that topic. The ideas of reducing the pain and suffering, enhancing the life quality, and accompanying and caring for the patient were present in most of the answers.

“Palliative care is the support, help and assistance given to patients in advanced diseases with near-death expectation, so that they have a better quality of life and comfort, and their suffering is reduced”,P1.“Palliative care is a treatment for chronic illnesses or those with a life expectancy of less than 6 months, which helps the patient to reduce pain and give them a better quality of life”,P2.“Caring to reduce the suffering of a person who is terminally ill”,P3.

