Finally, in the Moment 3, instead of asking for the definition one more time, the questionnaire included a variation of the same question: “What is the message you will carry with you regarding palliative care?”. The answers were very diverse, but a recurrent topic was the notion of palliative care as something people should have access to: “palliative care services are indispensable”, “everyone should have access to palliative care”, and “we all deserve to be cared for”. The PCKQ of Moment 3 also incorporated a new question: “Rate the need for training of future non-health professionals in the area of palliative care”. The possible answers were a scale that went from “very necessary” to “not necessary at all”. From the 21 respondents, 16 said rated palliative care knowledge as “very necessary”. 4 respondents said it was “necessary”. The only respondent left said it was both “necessary” and “very necessary”. Thus, by the end of the course, most of the students highly regarded the training they have received, and they valued it enough to consider it necessary for other students like them.

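### The only like-for-like change in students' definitions was measured across Module I, in at most 12 students, yet the conclusions report it for the whole course

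*Protocol article*

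**What the plan says.** **Timing.** Section 3.4.2 fixes the second questionnaire: "Following the end of Module I, students will receive links to the PCKQ and TECA of Moment 2". Section 4.1 gives the times as run: "before it started (Moment 1), after the first module (Moment 2), and during the last class (Moment 3".

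**What was analysed.** Section 4.1 describes four multi-select items and one open item asking for a definition of palliative care. The reported analysis is narrower: "The analysis carried out is centered on the open question and only took into consideration respondents who answered at the 3 Moments". Of the 25 students who agreed to take part, "12 students responded in Moment 1, 25 responded in Moment 2 and 21 responded in Moment 3".

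**The change at Moment 3.** Section 4.1 then reports that, "instead of asking for the definition one more time, the questionnaire included a variation of the same question". The new item asked which message about palliative care the student would take away.

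**What is concluded.** The conclusion of the abstract says that students' understanding changed. Section 7 says the same of the pilot as delivered to 29 students, in more cautious terms. Section 5.1 answers research question 1 with "Educational innovation seems to be a tailored solution to the communication necessities of palliative care".

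**Module content.** In Module I (section 2.3.1), "through flipped classes, the students will receive the theory required to face the rest of the course", in three groups. Module II (2.3.2) is a self-learning circuit modelled on an escape room, in groups of six. Module III is community service and Module IV a rhetoric seminar. Section 4.3 says of the professors: "Two of them gave theory classes in the Module 2, where the groups where smaller".

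**The concern.** A before-after comparison can speak only to what happened between its two measurements, and only if the same thing is measured at both. Here the same question was put to students at Moments 1 and 2 alone. The escape room, the community service and the rhetoric seminar all come after Moment 2, so a change in definitions seen at Moment 2 cannot reflect them.

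The conclusions do not carry this limit. A reader of the abstract or of section 7 would take the change as an outcome of the four-module course. Section 3.2 says that pilot feedback will be used to improve the course before it goes to other universities. Those who redesign it need to know that the definition data are silent on three of its four modules. They also need to know that the answer to research question 1 in section 5.1 does not draw on the pilot's data.

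**Working it through.** The plan states no sample-size or power figure on this point, so there is none to reproduce. The check sets timing, questions and respondents side by side.

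**1. Which question was asked, and when (sections 3.4.2 and 4.1)**

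| Moment | Time | Open question | Modules since the previous Moment |
|---|---|---|---|
| 1 | before the course | definition | none |
| 2 | after Module I | definition | I |
| 3 | last class | message taken away | II, III, IV |

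The definition item was used at 2 of 3 Moments. Modules between those two: 1 of 4. Modules outside the comparison: 4 − 1 = 3.

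**2. Can Moment 3 stand in for a repeated definition?** Section 4.1 calls its item a variation of the same question, but the recurring theme it reports at Moment 3 is that people should have access to palliative care. That is a view about provision and does not show what the student thinks palliative care is. A difference between Moments 2 and 3 therefore mixes a change in the student with a change in the question.

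**3. How many students (section 4.1)**

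Inputs: 25 participants; 12 respondents at Moment 1, 25 at Moment 2, 21 at Moment 3. All 25 answered at Moment 2, so the three-Moment set is the overlap of Moments 1 and 3.

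- Lower bound: 12 + 21 − 25 = 8.
- Upper bound: min(12, 21) = 12.
- As a share of participants: 8/25 = 32% to 12/25 = 48%.
- As a share of the 29 enrolled: 8/29 = 28% to 12/29 = 41%.

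Section 6 says that some answers were excluded because codes were forgotten or duplicated, without giving a number. After those exclusions 12 remains the ceiling, but the count may fall below 8.

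**4. What section 5.1 rests on.** Results from section 4 cited there: 0. The argument is that the course moves away from one-way messaging, lets students see care at first hand and talk with carers, and aims at lasting learning. The verbs express belief, intention and appearance.

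**5. Other evidence on the later modules.** None of what is reported gives a like-for-like change across Modules II to IV:

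- Moment 3 messages and training-need ratings (21 respondents): one time point only.
- Message Transmission Experiment: two guests, who were not course students, with no baseline definition reported.
- Focus group: three students, so far summarised from field notes.

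**6. The module label.** Section 4.3 places small-group theory classes in Module 2. Sections 2.3.1 and 2.3.2 place theory in Module I and the self-learning circuit in Module II. Sections 3.4.2 and 4.1 agree that Moment 2 follows Module I, so the label does not affect steps 1 to 3.

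**The case against.** The strongest reply is that these are preliminary results and are presented as such. Section 7 says that results suggest and hint, that empathy and mid-term results are pending, and that the separate teaching strategies need closer study. The research questions concern the course as a whole, and attributing change to modules is not a stated aim. This stands as a reason for restraint. It does not remove the point, because no caveat tells the reader that the comparable definition data end after Module I, and the abstract's statement of change is unqualified.

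The four multi-select items might also supply a comparison over the full course. That is possible, but their results are not reported and the article does not say whether they were unchanged at Moment 3.

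Three stronger readings are tempting, and the article does not support them:

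- *A reader might infer that research question 1 is answered with evidence on the wrong component.* Section 5.1 cites no questionnaire result. Module I is also taught by flipped classes in small groups and is itself part of the innovation. It is one component of four, and a change after it bears on the question in part.
- *A reader might infer that Modules II to IV have only the shared Moment 3 questionnaire.* Sections 3.4.2 and 3.4.3 also collect the Module II debriefing, the Module III reflection and the Module IV speeches.
- *A reader might infer that feedback was assigned to the wrong module.* The description in section 4.3 (theory, smaller groups) points to Module I, and the professors' reported comments are mostly about the course in general. The label is a minor discrepancy.

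**Conclusion.** The point holds in a limited form. The only reported like-for-like comparison of students' definitions covers one module of four, in 8 to 12 students before code exclusions and never more than 12. The abstract and section 7 report changed understanding for the course without that limit. The answer to research question 1 in section 5.1 is unsupported by pilot data; it is not contradicted by them. Nothing here shows that Modules II to IV add nothing: their effect on the definitions is simply unmeasured.

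This assumes that students answered the Moment 2 questionnaire before they took part in Module II, as sections 3.4.2 and 4.1 imply, and that the respondents at each Moment all belong to the 25 participants.

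**What to change.** 1. **Abstract conclusion and section 7.** State that the comparable change in definitions was measured after Module I only, give the number of students analysed, and say that any further change over Modules II to IV has not been shown. Cost: rewording, and a more modest conclusion.
2. **Section 5.1.** State that the answer to research question 1 rests on the design rationale of the course and not on pilot data. Cost: one sentence.
3. **Later editions.** Ask the identical definition question at Moments 3 and 4, and keep the message question as an addition. This gives a within-student comparison over the whole course and at five months, provided that codes can be linked. Cost: one more open question per questionnaire. Without a control group (section 6) and with modules in a fixed order, it would show change over the course and would not isolate the effect of any one module. Adding prompts to the escape-room debriefing would not replace it, since spoken group answers cannot be followed within a student.
4. **Section 4.3.** Reconcile the Module 2 label with sections 2.3.1 and 2.3.2. Cost: a minor correction.

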### 5.2 Research question 2: Can students help amplify the palliative care message?

This project perceives students of the Core Curriculum who are not in the health sector as potential re-transmitters of the palliative care message to society. If the information learnt through the course resonates with the students, they can potentially serve as a conduit to amplify the palliative care message as a result of the students’ high connectivity [24, 33]. High connectivity, or the ability to bridge multiple groups because of the formation of weak-tie relationships, allow the students to take what they have learnt in the course and share it with a wide variety of different audiences [33, 34]. Not only they may share it with other students in their degrees who didn’t enroll in this optative, but also with their family, friends and acquittances outside of the university environment.

Thus, we believe Care and Society used education as creative outlet that utilized rapid testing of multiple tools to create palliative care ambassadors in society. And we are also confident that these ambassadors are potential seeds of change, as they will be able both to send the message to multiple recipients and to react directly and immediately if they witness an incorrect portrayal of palliative care in their day-to-day life [25, 35]. This might potentially change the public opinion on palliative care in the long run.

## 6. Limitations

When launching the pilot, we decided not to have a control group. The two main reasons were: we did not consider the experience of a student taking Care and Society to be comparable to that of a student taking any other subject of the Core Curriculum offerings. And, secondly, the questionnaires themselves could lead to bias. By taking the same questionnaire repeatedly, it could generate curiosity in the control group participants, who might be able to acquire palliative care knowledge on their own and improve their performance in the following questionnaires. Nonetheless, for future attempts, we believe that the existence of a control group is advisable to rule out external change factors, such as exposure to news about the topic or to other media outlets.

The code system is another variable to take into consideration. As there is a time frame superior to a month in between moments of evaluation, some of the participants had a hard time remembering the city and the numbers they chose at the beginning of the pilot study. Furthermore, some of the participants chose the same city and the same combination of numbers. As a result, some of the answers had to be excluded from the preliminary results. In future attempts, a new system of codes might be helpful to improve the data recollection.

## 7. Conclusions

The preliminary results of the pilot, delivered to 29 students from degrees not related to health sciences, suggest that the understanding of the students about palliative care changed and some of the common misconceptions were clarified. Additionally, the overall impressions of the experience were positive. Both students and professors enjoyed the approach of the course and found its content useful and valuable for their day-to-day life. After completing the course, some of the students appeared to be able to explain what palliative care is to guest students with little or no experience in the topic. Nonetheless, in future evaluations more work needs to be done in assessing the efficiency of the message transmission. A more accurate assessment of the recipients’ previous knowledge on the topic needs to be carried out.

Furthermore, to evaluate if these students became ambassadors of palliative care an in-depth analysis of the course material and the results of the mid-term assessment are required. Up to now, the results hint that: (1) the students have improved their knowledge on palliative care, (2) they share a positive attitude regarding palliative care, and (3) they have started to communicate palliative care to their peers. But the mid-term assessment will show more definite results in the previous three aspects. In addition, it will provide us with insights regarding the permanence of the learning and the initiative of the students to advocate for palliative care if faced with a situation in which palliative care is being wrongly depicted. Further analysis is also needed to evaluate if the course generates a change in the levels of empathy. Moreover, the benefits of the different education strategies used in this course need to be studied in more detail.
